### Hypotheses

A. Effectiveness and comparison of the two treatments with the chronically depressed: Both psychotherapies lead to positive effects concerning (a) the reduction of depressive symptoms (QIDS, BDI), (b) the proportion of remitted patients (LIFE), (c) improved social functioning (SOFAS), (d) a decrease of continuous antidepressant medication. These effects are manifested at the main assessments (see Table 2: t4, t6, t8) a cross the trial. The courses of change differ between PAT and CBT: (a) CBT achieves faster symptom reduction, (b) PAT starts slowly but achieves more stable, lasting effects (this is evidenced in the process measures, the rates of response and the symptom level at follow-up (see Table 2: t6, t8, t10).

B. Comparison of preferred and randomized therapies: Preferred therapies are expected to lead to stronger effects and less study drop-outs than randomized therapies. Patient preference is particularly important in PAT. Therefore, we expect larger effect differences between PAT preference and PAT randomization compared with CBT.

C. Health costs and cost effectiveness. We expect a significant reduction of the days of absence from work and of further treatment needed (for example, hospitalization) for both therapies. We expect larger health-cost reductions for PAT compared with CBT in the long term. We expect that treatment costs for CBT will be lower than those for PAT, resulting in a better cost-benefit ratio.

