### Design

The trial will include about 360 chronically depressed outpatients. About 180 patients will have a clear preference foreither PAT or CBT. After baseline assessment (t0) they will be assigned to a study therapist offering the preferred intervention. About 180 patients will come without preference and accept to be randomized to either PAT or CBT. Randomization will take place after baseline assessment (t0). Figure1 summarizes the 2 (preference) by 2 (psychotherapies) by 4 (time) factorial design.

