### Outcome

The primary outcome measures are the Quick Inventory of Depressive Symptoms (QIDS [26]) (independent clinician rating) and the Beck Depression Inventory (BDI-2) one year after initiation of treatment (t4). Treatment response is defined as a decline of at least 50% from t0 (baseline, pre-treatment) to t4 (12 months after intake. Remission is defined by a QIDS-score below 6. A relapse is defined when the criteria of a major depressive disorder (MDD) are fulfilled, for example, a QIDS-score above 9 is documented or hospitalization or outpatient treatment are needed.

Secondary outcome measures include the Beck Depression Inventory (BDI 2 [27]), the QIDS-self-rating, the Symptom-Checklist (SCL-90R [28]), the Depressive Experience Questionnaire (DEQ [29]) and the Dysfunctional Attitude Scale (DAS [30]). Furthermore, we assess social functioning (SOFAS [31]), the Helping Alliance Questionnaire (HAQ [32], and recurrence of depressive episodes assessed by the longitudinal follow-up evaluation interview (LIFE [33]).

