### Secondary analyses

Self-report questionnaires and observer ratings will be analyzed by mixed models with repeated measurements. With two co-primary outcomes, we will conduct the tests at a 0.025 level of significance (two-tailed) to adjust for the multiple comparison issue. Further analyses will include cross-sectional analyses to compare therapists; subgroup analyses of subjects’ and therapists’ conditions; and costs of the SP treatment.

Descriptive statistics showing the measurements over time will be presented whenever appropriate. Serious adverse events and cases of drop-outs will be analyzed descriptively.

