### Statistical analysis

The design is an analysis of variance design with repeated measures: The main factor is the form of treatment (CBT or PAT) and assignment (preference or randomization). Four main assessments encompass the treatment phase and follow-up. The variability of intake symptoms is controlled as a covariate. To determine the time factor, ANCOVAs with repeated measures and linear regression with autocorrelated data (compound symmetric covariance structure models) are applied. Dichotomous response scores are examined by tests for frequency distributions and procedures of survival analysis (Coxregression, log-ranktests). It is also tested whether differences between CBT and PAT depend on assignment (preference vs. randomization), that is, if a naturalistic selection brings clearer differences than random assignment.

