## Discussion

This trial has the major goals: (1) to determine the effectiveness of the two long-term treatments (PAT, CBT) reimbursed in the German healthcare system for chronic depression, and (2) to compare the effects of treatment preference against randomization. It combines the virtues of a randomized controlled (efficacy) trial and a naturalistic approach.

As recent meta-analyses have shown, the treatment of depression by short-term treatments has been plagued by high relapse rates and a lack of lasting effectiveness. Long-term PAT and CBT, however, are not easy to compare, as they differ in frequency (one to three sessions per week), total number of sessions, and duration of treatment (one to three years). We therefore tried to reach comparable doses in the first year of treatment. Initially, psychoanalysts often work with low frequency (≤2 sessions per week) with depressed patients; thus there could be 45 sessions of CBT and up to 80 sessions of PAT in the first year. As our primary outcome is measured at one year (t4), doses of treatment can be compared. When psychoanalytic treatment is continued after one year, dose can be adjusted according to patient need and treatment process. As CBT entails relapse prevention, there will also be an extended treatment duration. In any case, number and timing of sessions will be documented. In this trial, a high quality is assured by an independent assessment.

While patient preferences form one of the three key components of evidence-based medicine, studies on the impact of patient preference on outcome have been scarce. Our design enables us to determine the impact of patient preference on outcome, and we expect a lower attrition rate and a higher effectiveness for preferred vs. randomized assignment.

As this trial has been funded substantially by the German Society for Psychoanalysis, Psychotherapy, Psychosomatics, and Depth Psychology (DGPT), a great effort was made to counteract allegiance effects. The study also is financially supported by the independent, medically oriented Heidehof Foundation (part of the well known Robert Bosch Foundation, Stuttgart). One of the principal investigators (MH) is a renowned cognitive behavior therapist. Data collection, monitoring, and analysis are performed by an independent statistician (BR).

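### The 0.025 co-primary test is not tied to the 12-month contrast it was sized for, and the stated compound symmetry can make tests of the course of change too liberal

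*Protocol article*

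**What the plan says.** The Outcome section places both primary measures, clinician-rated QIDS and BDI-2, "one year after initiation of treatment (t4"). The Discussion repeats this: "As our primary outcome is measured at one year (t4), doses of treatment can be compared". The Sample size calculation uses a single between-treatment difference, d = 0.50 at post-treatment, with two-tailed alpha 0.025 and power 0.80, and arrives at 60 per cell.

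The analysis is described in other terms. The Design section speaks of "the 2 (preference) by 2 (psychotherapies) by 4 (time) factorial design". The Statistical analysis section says "The main factor is the form of treatment (CBT or PAT) and assignment (preference or randomization"), and continues: "Four main assessments encompass the treatment phase and follow-up. The variability of intake symptoms is controlled as a covariate". For the time factor it adds that repeated-measures ANCOVAs and "linear regression with autocorrelated data (compound symmetric covariance structure models) are applied".

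The rule of 0.025 for each co-primary outcome appears only under Secondary analyses, next to a sentence about mixed models, and names no visit. Hypothesis A expects the treatments to follow different courses: CBT reduces symptoms faster, while "PAT starts slowly but achieves more stable, lasting effects".

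**The concern.** Endpoint and sample size refer to one visit; the stated model covers four. Its treatment term is a difference averaged over visits, and that equals the t4 difference only if the difference is constant. The trial's own hypothesis says that it is not.

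The visits are also open. Hypotheses lists three main assessments (t4, t6, t8). Table 2 labels four rows as main assessments (t4, t6, t8, t9), and its caption makes t7 to t10 dependent on funding. An averaged effect would therefore change its meaning with the extension that is funded.

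Two things are at stake. First, a real 12-month difference could be missed, or the analyst could choose between the averaged, interaction and t4 results after seeing them. Second, compound symmetry assumes the same correlation between visits one year apart and two years apart. If correlation decays with time, the tests of differing courses in hypothesis A reject too often.

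**Working it through.** **Plan's own figure.** n per group = 2(z₀.₉₈₇₅ + z₀.₈₀)²/d² = 2(2.241 + 0.842)²/0.25 = 76.04, so 77 (78 with the t distribution). The stated 60 does not follow from the stated inputs and gives power 0.69 for d = 0.50. That is a separate matter. I use 78 per group below only so that the t4 test starts near the intended 0.80.

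**Inputs.** From the protocol: alpha 0.025 two-sided, d = 0.50, and yearly visits t4, t6 and t8 (12, 24 and 36 months). Assumed: 78 per group, SD 1 at each visit, correlation 0.6 per year of lag (0.6, 0.6, 0.36), and the patterns of difference below (positive favours CBT).

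**Power: t4 contrast against the three-visit average.**

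- SE at t4 = √(2/78) = 0.160. Power = Φ(0.5/0.160 - 2.241) = Φ(0.88) = 0.81.
- Variance factor of the average = [3 + 2(0.6 + 0.6 + 0.36)]/9 = 0.68. SE = √0.68 × 0.160 = 0.132.

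| Difference at t4 / t6 / t8 | Average | Average/SE | Power, average | Power, t4 |
|---|---|---|---|---|
| +0.5 / +0.5 / +0.5 | 0.50 | 3.79 | 0.94 | 0.81 |
| +0.5 / +0.25 / 0 | 0.25 | 1.89 | 0.36 | 0.81 |
| +0.5 / +0.1 / -0.3 | 0.10 | 0.76 | 0.07 | 0.81 |

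A larger sample does not remove the gap. At 120 per treatment, t4 power is 0.95, against 0.54 (fading) and 0.10 (reversing) for the average. With a stronger late reversal the sign changes: (0.5 - 0.5 - 0.5)/3 = -0.17.

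**Compound symmetry and the t4-to-t8 contrast.** Take the common correlation as the mean of the three true ones.

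- Yearly correlation 0.6: common value (0.6 + 0.6 + 0.36)/3 = 0.52. Variance of the within-patient change: true 2(1 - 0.36) = 1.28, assumed 2(1 - 0.52) = 0.96. SE ratio = √(0.96/1.28) = 0.866. Actual level = 2[1 - Φ(2.241 × 0.866)] = 0.052.
- Yearly correlation 0.8: common value (0.8 + 0.8 + 0.64)/3 = 0.747. SE ratio = √(0.253/0.36) = 0.839. Actual level = 2[1 - Φ(2.241 × 0.839)] = 0.060.

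A simulation (10,000 runs, 60 per group, complete data, yearly correlation 0.6) gave 0.052 to 0.055 for this contrast. The averaged main effect stayed at 0.023 to 0.026. A t4 contrast taken from the compound-symmetry fit held its level with equal variances. It ran at 0.004 to 0.005 when the SD rose from 0.8 to 1.2 over the visits, and at about 0.055 when it fell from 1.2 to 0.8.

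**The case against.** The strongest reply is that no sentence makes the averaged treatment effect the primary test. A reader might infer that it does from the description of treatment as a main factor, but that phrase names a design factor. A 2 × 2 × 4 layout also contains treatment-by-time terms, and Outcome and Discussion fix the endpoint at t4. This stands: the defect is that the primary test is not tied to t4, not that a wrong test has been declared.

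Four other stronger readings are tempting and also go too far:

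- *The averaged effect must cancel.* Hypothesis A gives directions only, with no sizes and no crossing time, and CBT's early lead could fall before t4. Shrinkage or a change of sign is possible, not certain; a constant difference would gain power.
- *Compound symmetry spoils the averaged effect.* In complete balanced data it does not; the harm falls on contrasts between visits and, if variances change, on single-visit contrasts.
- *Patients with a missed visit are dropped.* The mixed models under Secondary analyses cover self-reports and observer ratings, so they can include both co-primary instruments. Listwise deletion is not established, and no dropout rate is given.
- *Intake is both outcome and covariate.* Neither Hypotheses nor the labels in Table 2 count t0 among the main assessments. Only the failure to name the four visits leaves this open.

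An article may also leave therapist effects to a fuller plan. This one mentions only "cross-sectional analyses to compare therapists" and gives no caseload or intraclass correlation. With 2 to 6 patients per therapist and a correlation of 0.02 to 0.10 (all assumed), ignoring therapists would move 0.025 to between 0.027 and 0.067. The direction is sound; the size is assumption.

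**Conclusion.** The point holds in this form. The endpoint and sample size concern t4, but the stated model is over four unnamed visits, and nothing ties the 0.025 test to a t4 contrast. If its treatment term were used as the test, it would not estimate the t4 difference under the changing courses that the trial expects. In the assumed patterns, power falls from 0.81 to 0.36 or 0.07, while a constant difference would raise it to 0.94. Those figures rest on the assumed patterns, 78 per group and a yearly correlation of 0.6.

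The covariance choice is more than an omitted detail, because compound symmetry is stated explicitly for the time factor. If the yearly correlation is 0.6 to 0.8 and decays with lag, the t4-to-t8 treatment contrast runs at about twice its nominal level (0.052 to 0.060 against 0.025). If correlation does not decay and variances are equal, the level is correct.

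**What to change.** For each co-primary outcome, state that the PAT-CBT contrast at t4 is the single confirmatory test at two-sided 0.025. Take it from a mixed model with treatment-by-visit terms and named post-baseline visits (t4, t6 and t8, as available). Use the t0 score only as a covariate, and unstructured covariance in place of compound symmetry. Report the t4-to-t8 contrast from the same model as the test of differing courses. A random intercept for therapist is a sensible supporting addition.

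The cost is analysis wording only, since mixed models are already named in the article. Intervals may be slightly wider with the therapist term. If the difference proves constant, the t4 test gives up the power that averaging would have gained. The article reports recruitment as ongoing, so the test can be fixed before results are known.

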So far, the evidence for psychotherapy of depression rests on short-term treatments [6-8]. Unlike the results for the treatment of acute depression, psychotherapy, findings of the effects for chronic depression (dysthymia or major depressive episodes) have been limited [8]. In addition, short-term treatments offered in randomized controlled trials lack external validity. Unlike the treatments performed in clinical trials, psychotherapies in clinical practice throughout Europe are of considerably longer duration (CBT up to 60 sessions, psychodynamic treatment up to 80, psychoanalysis up to 240 to 300 sessions). Positive long-term effects of psychoanalysis and psychoanalytic long-term treatments were shown in a representative, multi-perspective and retrospective study [9]. Yet, up until now, there are no controlled studies available comparing psychoanalysis (PAT) and cognitive behavior therapy (CBT) directly [10,11]. However, a few clinical reports [12] comparing psychoanalytic and cognitive-behavioral long-term therapy exist. They demonstrate that even when psychoanalysts and behavior therapists treat similar disorders with similar success rates, the patients differ in many ways.

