### Assessments

The time points of assessment and the measures are presented in Table 2. Assessment is conducted before assignment to treatments, and over a course of three years. Patients are assessed (structured clinical interview, SCID; quick inventory of depressive symptoms, QIDS) by independent and trained clinicians, who are blind to treatment conditions. We took great care to characterize patients by psychoanalytically oriented characteristics of psychic structure and conflict [23-25].

**Table 2 T2:** Planned assessments in the course of the trial (t7 to t10 are options for extension, depending on funding)

**Measure point**	**Patient**	**Therapist**	**Diagnostician**
**t0 intake**	BDI-2, SCL90-R, DAS, DEQ, CTQ, IIP		SKID I/II, QIDS-C, OPD-2, HUS, SRS, SOFAS
t1 (weekly, weeks 1–6)	QIDS-S, HAQ	QIDS-C, HAQ	
t2 (3 mo)	QIDS-S, HAQ	QIDS-C, HAQ	
t3 (6 mo)	QIDS-S, HAQ	QIDS-C, HAQ	
**t4 main assessment (12 mo)**	BDI-2, SCL-90R, DAS, DEQ, IIP, HAQ	QIDS-C, HAQ	LIFE, QIDS-C, OPD-2, HUS, SRS, SOFAS
t5 (18 mo)	QIDS-S, HAQ	QIDS-C, HAQ	
**t6 main assessment (24 mo)**	BDI-2, SCL-90R, DAS, DEQ, IIP, HAQ		LIFE, QIDS-C, HUS, SRS, SOFAS
t7 (30 mo)	QIDS-S, HAQ	QIDS-C, HAQ	
**t8 main assessment (36 mo)**	BDI-2, SCL-90R, DAS, DEQ, IIP, HAQ	QIDS-C, HAQ	LIFE, QIDS-C, OPD-2, HUS, SRS, SOFAS
**t9 main assessment (48 mo)**	BDI-2, SCL-90R, DAS, DEQ, IIP, HAQ		LIFE, QIDS-C, HUS, SRS, SOFAS
**t10 final assessment (60 mo)**	BDI-2, SCL-90R, DAS, DEQ, IIP, HAQ		LIFE, QIDS-C, OPD-2, HUS, SRS, SOFAS

Notes: *BDI 2* Beck Depression Inventory II, *CTQ* Childhood Trauma Questionnaire, *DAS* Dysfunctional Attitude Scale, *DEQ* Depressive Experience Questionnaire, *HAQ* Helping Alliance Questionnaire (patient-, therapist-form), *HUS* Heidelberger Restructuring Scale, *IIP* Inventory of Interpersonal Problems, *LIFE* Longitudinal Follow-up Evaluation, *OPD-2* Operationalized Psychodynamic Diagnostics, *PEI* Psychoanalytic Intake Interview, *QIDS* Quick Inventory of Depressive Symptoms [self- (QIDS-S) and clinician-rating (QIDS-C)], *SCID I, II* Structured Clinical Interview according to DSM-IV, *SCL-90R* Symptom-Checklist, *SOFAS* Social functioning, *SRS* Self-Reflective Functioning Scale.

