### Sample size calculation

Sample size calculation was based on meta-analyses with similar interventions in similar patient groups using similar outcome instruments [10,11,34,35]. Based on the Hamilton Depression Rating Scale (a 17-item clinician rating form, similar to the QIDS-C) we expect pre-post effect sizes for psychotherapies of depression of *d* = 1.2. A study including a direct comparison of PAT and CBT is not available. Therefore, we used meta-analysis of comparing psychotherapy with psychiatric therapy with depressed out-patients to extrapolate a probable effect size of *d* = 0.50 between treatments of different efficacy at post-treatment. To detect this difference at *α* = 0.025 (two-tailed) with a power of 0.80, a minimum number of 60 patients per cell are required (see Figure1).

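### The comparisons that rest on patient choice are adjusted only for intake symptoms, although t0 already measures diagnosis, personality disorder, trauma and functioning

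*Protocol article*

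**What the plan says.** The Statistical analysis section describes a repeated-measures analysis with form of treatment and form of assignment as factors. On adjustment it says: "The variability of intake symptoms is controlled as a covariate". It does not name the scale or scales meant. It also plans to test whether the PAT-CBT difference depends on assignment.

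Under Randomization, patients who state a preference receive the preferred therapy, and only those without one are randomized. The Design section expects about half of the sample in each arm. The effect of preference is hypothesis B and one of the two major goals named in the Discussion.

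Table 2 (Assessments) lists what is collected at t0, before assignment. From the patient: "BDI-2, SCL90-R, DAS, DEQ, CTQ, IIP". From the diagnostician: "SKID I/II, QIDS-C, OPD-2, HUS, SRS, SOFAS". Secondary analyses mentions subgroup analyses by patient and therapist conditions, but no further adjustment of the main contrasts.

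**The concern.** Randomization protects the PAT-CBT comparison in the randomized arm only. Within the preference arm, those who choose PAT may differ from those who choose CBT in diagnosis, personality pathology, trauma history or functioning. Patients with a firm preference may likewise differ from those without one. An intake symptom score captures such differences only as far as they show in current severity. The remainder goes into the estimated therapy or preference effect. Because both arms share one model, a treatment main effect pooled over them also carries part of any bias from the preference arm.

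What is at stake is the preference hypothesis and the test of whether the PAT-CBT difference depends on assignment. A finding there could reflect who chose rather than what choosing or the therapy did. The measures that would reduce this are already collected.

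**Working it through.** **Inputs from the protocol article**
- Significance level: "we will conduct the tests at a 0.025 level of significance (two-tailed"), for each of two co-primary outcomes (Secondary analyses).
- Planned effect: d = 0.50 "between treatments of different efficacy at post-treatment" (Sample size calculation).
- Group sizes: the Abstract gives 240 patients, 60 per arm, so 60 v 60 within the preference arm and 120 v 120 for preference versus randomization. The Design section gives about 360, 180 in each arm, so 180 v 180 for preference versus randomization and, if the preference arm splits evenly, 90 v 90 within it. Both totals are carried below.

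**The plan's own figure.** The article says "a minimum number of 60 patients per cell are required", "two-tailed) with a power of 0.80". Unadjusted, n = 2(z₀.₉₈₇₅ + z₀.₈₀)²/d² = 2(2.2414 + 0.8416)²/0.25 = 76.04, so 77 per cell. At 60 per cell, power is Φ(0.50·√30 − 2.2414) = Φ(0.497) = 0.69. The stated 60 is not reproduced. It would follow if covariates explained 1 − 60/76.04 = 21% of outcome variance, which the article does not state. This is a separate matter and the bias calculation does not depend on it.

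**Assumptions, not given in the documents.** After adjustment for intake symptoms, an omitted baseline variable differs between the groups by 0.2 to 0.5 SD, and its partial standardized effect on the outcome is 0.1 to 0.3.

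**Bias** = imbalance × partial effect.
- Low: 0.2 × 0.1 = 0.02 SD, which is 4% of d = 0.50.
- High: 0.5 × 0.3 = 0.15 SD, which is 30% of d = 0.50.
- Pooled PAT-CBT effect: if the two arms carry equal weight and the randomized arm is unbiased, the bias is half of this, 0.01 to 0.075 SD.

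**False-positive rate when there is no true difference** (outcome SD = 1, normal approximation). With δ = bias × √(n/2), the rate is 1 − Φ(2.2414 − δ) + Φ(−2.2414 − δ).

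| Contrast | n per group | δ, low to high | Rate (nominal 2.5%) |
|---|---|---|---|
| PAT v CBT, preference arm | 60 | 0.110 to 0.822 | 2.6% to 7.9% |
| PAT v CBT, preference arm | 90 | 0.134 to 1.006 | 2.6% to 10.9% |
| Preference v randomization | 120 | 0.155 to 1.162 | 2.7% to 14.0% |
| Preference v randomization | 180 | 0.190 to 1.423 | 2.8% to 20.7% |

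The low end is almost nominal. At a fixed bias the rate rises with n, because the standard error shrinks and the bias does not.

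**Precision in the randomized arm.** If r is the correlation of intake score with outcome and further covariates add explained variance e, the standard error is multiplied by √[(1 − r² − e)/(1 − r²)]. Both r and e are assumptions. With e = 0 there is no gain. With r = 0.5, e = 0.03 gives √(0.72/0.75) = 0.980 and e = 0.10 gives √(0.65/0.75) = 0.931, a fall of 2.0% to 6.9%.

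**The case against.** The strongest reply is that the article does not say that intake symptoms are the only covariate, and that a full list commonly belongs in an analysis plan that is not shown. This stands in part: no omission can be charged. But the article does print an adjustment for a model that contains the preference factor, and that stated choice can be judged.

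A second reply is that selection is part of the question, since the protocol asks whether therapies differ more clearly when patients choose, and adjustment removes some of what is studied. This also stands. It is a reason to show both models, not to show the intake-only model alone.

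Third, every imbalance and effect above is assumed, and the low end is harmless. That is correct.

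Readers might also infer three stronger things that the documents do not support:
- *That the second co-primary scale is left out.* The wording on intake symptoms names no scale and may already cover both QIDS-C and BDI-2.
- *That the protocol admits selection in its own sample.* The Background remark that "the patients differ in many ways" comes from outside clinical reports on psychoanalytic and cognitive-behavioral patients with similar disorders and similar success rates. It makes selection plausible for PAT versus CBT. It shows no imbalance in this trial and says nothing about preference versus randomized patients.
- *That the randomized comparison is damaged.* Leaving out baseline covariates does not bias it. The precision lost depends on figures the documents do not give and may be close to zero.

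**Conclusion.** The point holds for the contrasts that rest on patient choice. The stated adjustment leaves characteristics measured at t0 uncontrolled in preference versus randomization, in PAT versus CBT within the preference arm, and in part in any pooled treatment effect. The size can be given only as a range under the assumptions above. It runs from negligible to a bias of 0.15 SD, or 30% of the planned effect, with a false-positive rate of up to about 8% to 21% depending on contrast and total sample size. It does not hold as a criticism of validity in the randomized arm, and no precision loss there can be established. This is a worthwhile, inexpensive improvement to a major goal of the trial, not a defect in its randomized comparison.

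**What to change.** For the by-choice contrasts at t4, prespecify adjustment for t0 QIDS-C and BDI-2, SCID diagnosis (major depression or dysthymia), SCID II personality disorder, CTQ, SOFAS, IIP, DEQ and DAS, entered directly or through a propensity score. Show the intake-only model beside it, since that model keeps the naturalistic selection the protocol also asks about. Report these contrasts as adjusted observational comparisons.

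Base the PAT-CBT efficacy conclusion on the randomized arm. A short prespecified set there (both co-primary baselines and diagnosis) is optional, for precision only. State in either case which scale or scales the intake-symptom covariate means.

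The cost is a few degrees of freedom, one more model per outcome, and simple imputation of occasional missing t0 values. No new data are needed. Unmeasured reasons for choice remain uncontrolled, and the report should say so.
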